### **Visits 3 and 4 (Weeks 1 and 2)**

These visits will assess blood pressure and any subject-reported adverse events 7 and 14 days, respectively, following initiation of telmisartan. No laboratory evaluations will be performed unless prompted by adverse events.

### **Visit 5 (Week 6)**

A targeted physical exam (including blood pressure measurement) and safety laboratory evaluations will be performed.

### **Visit 6 (Week 12)**

This visit will include a targeted physical exam, safety laboratory evaluation, and the collection of stored serum, plasma, and urine samples for future analyses.

### **Visit 7 (Week 18)**

A targeted physical exam and safety laboratory evaluations will be performed.

### **Visit 8 (Week 24)**

This visit will be the final study visit. A targeted physical exam, safety laboratory evaluation, and the collection of banked serum, plasma, and urine samples will be performed. A single 5 mm slice CT scan at the level of L4-L5 will be scheduled within 14 days of this visit, and the image will be sent to the central reading center in electronic format. After this visit, telmisartan will no longer be provided by the study. However, should a subject wish to continue to take telmisartan, he or she may do so by prescription from their primary care provider.

### **6.3 Pregnancy**

Subjects who become pregnant after study entry must discontinue study treatment immediately. Subjects will continue to be followed on study but off study treatment as per the Schedule of Events in Section 6.1, except for CT scans. Pregnancies that occur on study should be reported to The Antiretroviral Pregnancy Registry. Reporting forms can be found in the Manual of Operations (MOP). More information is available at [www.apregistry.com](http://www.apregistry.com). [contact]; [contact].

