## **4.0 SELECTION AND ENROLLMENT OF SUBJECTS**

### **4.1 Inclusion Criteria**

- 4.1.1 HIV positive men and women age 18 and older.
- 4.1.2 HIV-1 infection, as documented by any licensed ELISA test kit and confirmed by Western blot at any time prior to study entry or plasma HIV-1 RNA > 2000 on two occasions.
- 4.1.3 Documented central fat accumulation (defined for women/men as: waist circumference > 94/95 cm or a waist-to-hip ratio > 0.88/0.94).
- 4.1.4 HIV-1 RNA documented to be less than 50 copies/mL at screening and undetectable by assay of choice (<50 or <400) for at least 12 weeks prior to entry.
- 4.1.5 Current antiretroviral therapy with a suppressive, highly active anti-retroviral regimen. Subjects must not have changed ART in the 12 weeks prior to entry, and must not be planning to change ART for the 24 week study duration.
- 4.1.6 Systolic blood pressure >115mmHg. Telmisartan has been demonstrated to be safe for use in normotensive subjects.
- 4.1.7 Ability and willingness of subject to provide informed consent.

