### **8.2 Premature Study Discontinuation**

- Request by the subject to withdraw.

- Request of the primary care provider if he or she thinks the study is no longer in the best interest of the subject.
- Subject judged by the investigator to be at significant risk of causing harm to self.
- At the discretion of the IRB, Food and Drug Administration (FDA), Office for Human Research Protections (OHRP), investigator, or the pharmaceutical sponsor.

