### **8.3 Early Discontinuation**

Any subject who develops a Grade 3 or 4 symptom or laboratory abnormality (other than cholesterol, and triglycerides), UNLESS THE INVESTIGATOR HAS A COMPELLING REASON TO THINK IT IS NOT RELATED TO TELMISARTAN) will be evaluated and will have study treatment withheld until the toxicity resolves ( $\leq$  grade 2). If the abnormality is thought to be related to study treatment, the subject will not be re-challenged without discussion with protocol chairs (see Sections 7.2, 7.3). Subjects requiring premature study discontinuation will undergo a final safety evaluation and CT scan. Serum and plasma will also be banked at the time of study discontinuation (in lieu of the Week 12 or Week 24 sample). All subjects will remain in follow-up for resolution of Grade 3 or 4 toxicities.

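### The exit CT in Section 8.3 has no pregnancy exception, and the CT exemption in Section 6.3 is worded only for the Section 6.1 schedule

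*Protocol*

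**What the plan says.** Four parts of the Protocol bear on this point.

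- **Section 6.3 (Pregnancy).** "Subjects who become pregnant after study entry must discontinue study treatment immediately". She then stays on study, off drug, "as per the Schedule of Events in Section 6.1, except for CT scans". On reporting, the section says: "Pregnancies that occur on study should be reported to The Antiretroviral Pregnancy Registry". The forms are held in the Manual of Operations.
- **Section 6.1 (Schedule of Events).** The CT row has two entries, Baseline and Week 24. The table has no column for an early exit visit.
- **Sections 8.1 and 8.2.** Pregnancy is listed in 8.1 among the reasons for permanently stopping study drug. It is not among the reasons in 8.2 for leaving the study. Two entries in 8.2 could readily apply to a pregnant subject: "Request by the subject to withdraw" and "Request of the primary care provider if he or she thinks the study is no longer in the best interest of the subject".
- **Section 8.3 (Early Discontinuation).** "Subjects requiring premature study discontinuation will undergo a final safety evaluation and CT scan". The sentence carries no exception and does not point back to 6.3.

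**The concern.** The two CT provisions do not meet. Section 6.3 waives CT in pregnancy but words the waiver as a departure from the 6.1 table. The exit CT is not in that table; it is created in 8.3. A pregnant subject who completes follow-up is therefore spared the Week 24 scan, while one who leaves before Week 24 is, on the literal text, still due a scan.

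What is at stake is patient safety: an avoidable abdominal CT in a pregnant woman. The question for the analysis is whether the scan would serve any planned purpose that might justify it.

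**Working it through.** The protocol gives no figure on this point to reproduce, so the check is mainly a reading of the sections against each other.

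**Step 1: does the 6.3 exemption reach the exit CT?** It modifies follow-up under the 6.1 schedule. That schedule contains two CTs, Baseline and Week 24, and the Baseline scan precedes drug. For a subject who becomes pregnant after entry, the exemption as worded removes one scan, at Week 24. The exit CT lies outside the schedule, so the wording does not cover it.

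**Step 2: does pregnancy by itself trigger the exit CT?** No. Section 8.1 makes pregnancy a reason to stop drug, and 6.3 keeps the subject on study. Section 8.3 attaches the scan to premature discontinuation of the study, the same term as the heading of 8.2.

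**Step 3: can a pregnant subject reach 8.3?** Yes, by a second event. She may withdraw, or her primary care provider may ask for her withdrawal in her interest. Either is plausible once the study drug has been stopped.

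**Step 4: would the scan be used?**

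- *Primary analysis (9.6.1).* It is as-treated and excludes subjects who do not remain on the study regimen. Those off telmisartan for 14 or more consecutive days also stop contributing from the date they stopped. A pregnant subject is permanently off drug, so her exit scan cannot enter.
- *Supplementary intent-to-treat analysis (9.6.1).* This is the only planned VAT analysis the scan could feed. The visible text does not say how an early scan would be handled there.
- *Comparison with those who stay.* A pregnant subject who stays to Week 24 has no follow-up CT either, by 6.3. The plan already accepts losing that observation.

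**Step 5: size.** The planned enrolment is 35 (9.1). Assume 0 or 1 pregnancy, since 4.2.1 requires contraception where pregnancy is possible; the protocol gives no rate. The number of exit scans at issue is then 0 or 1, and is 1 only if that subject also leaves early. Excepting her removes at most 1 of 35 observations from the supplementary analysis: 1/35 = 2.9%. The primary analysis loses 0.

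**Step 6: can the subject be identified in time?** Section 6.6 requires a pregnancy test at each safety evaluation time point for women of reproductive potential, and 8.3 pairs the CT with a final safety evaluation. The test is therefore already due. The text does not say that its result must be known before the scan.

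**The case against.** The best reply is that 6.3 is the specific rule for pregnant subjects and 8.3 the general rule for leavers, so the specific rule should govern. The trial has one site (Section 14.0), the protocol chairs review study discontinuations (9.5), and a withdrawing subject may decline the scan. Harm needs a pregnancy despite contraception, an early exit, and staff who overlook 6.3.

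Most of this stands. The intent of 6.3 is clear and the chance of harm is small, so this is a gap in wording and not a flat contradiction. It does not remove the point. The exemption is expressly tied to the schedule, 8.3 is unqualified, and a procedure in a pregnant subject should not depend on staff inferring which section prevails.

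A reader might go further and infer that the study neglects the outcome of a pregnancy exposed to telmisartan. The documents do not support that. Section 6.3 provides for on-study follow-up and for a registry report, and says "Reporting forms can be found in the Manual of Operations (MOP". Section 8.3 also keeps all subjects in follow-up until Grade 3 or 4 toxicities resolve. The Manual of Operations and the consent form are not available, so a missing outcome contact cannot be shown. Asking the study to run a second contact beside the registry would be a preference.

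**Conclusion.** The point holds in a narrow form. Section 8.3, read literally, sends a pregnant subject who leaves the study early for an abdominal CT, because the 6.3 exemption covers only the scheduled scans. That scan has no place in the primary analysis.

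The conclusion rests on the wording of 6.1, 6.3, 8.1 to 8.3 and 9.6.1. The only assumption is the likely count, 0 or 1 pregnancy among 35 subjects. If the count were higher, the wording gap would be the same and would matter more.

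Two stronger readings should be avoided. Pregnancy alone does not lead to the exit CT, because the subject stays on study. Nor does the gap bias any result: the sample size, power and primary analysis are untouched, and the supplementary intent-to-treat analysis loses at most one observation. This is a low-priority safety correction worth making because it is so cheap.

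**What to change.** In Section 8.3, change the end of the exit sentence so that the safety evaluation is followed by: *and, except in pregnant subjects, a CT scan*. Add that the pregnancy test due at that evaluation under 6.6 is read before any CT is performed.

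The cost is a short clause and one ordering instruction. The test itself is already required, so no visit or procedure is added. One intent-to-treat observation may be forgone, which 6.3 already accepts for a pregnant subject who stays to Week 24. The amendment goes through the usual IRB review under 11.1.

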### **6.4 Discontinuation Evaluations**

#### Evaluations for Registered Subjects Who Do Not Start Study Treatment

Subjects who do not start study treatment will be taken off study without further evaluation. The subject will be replaced. All case report forms (CRFs) must be completed and keyed for the period up to and including week 0.

#### Premature Study Treatment/Background ART Discontinuation Evaluations

Subjects who discontinue telmisartan due to adverse events or by personal choice will be followed and asked to complete the Week 12 and Week 24 evaluations (as listed in the Schedule of Events (section 6.1)) prior to being taken off study.

Subjects who discontinue their background ART entry regimen for  $\geq 14$  consecutive days due to toxicity or adherence will be asked to complete the Week 12 and Week 24 evaluations prior to being taken off study.

Subjects experiencing drops in systolic blood pressure below 100mmHg (without sequelae) or asymptomatic increases in serum creatinine, AST, ALT, or alkaline phosphatase (to  $<3\times$  ULN for liver enzymes) may temporarily discontinue telmisartan. When systolic blood pressure returns to  $>100\text{mmHg}$  and/or if laboratory abnormalities resolve within 14 days, telmisartan may be restarted at the discretion of the study physician and subject at a dose of 20 mg po daily. The subject should be monitored closely for tolerability. If the subject does not experience a recurrence of the adverse event, he/she may continue on telmisartan for the duration of the study.

### **6.5 Clinical Assessments**

#### Documentation of HIV

HIV-1 infection, as documented by any licensed ELISA test kit and confirmed by Western blot at any time prior to study entry. HIV-1 culture, HIV-1 antigen, plasma HIV-1 RNA, or a second antibody test by a method other than ELISA are acceptable alternative confirmatory tests. This does not need to be recorded on a CRF, but a copy should be placed in the subjects study chart for documentation.

#### Documentation of Virologic Suppression

HIV-1 viral load at screening must be less than 50 copies/mL. Documentation should be provided in the study chart that the subject has had an undetectable viral load for at least 12 weeks prior to entry, but does not need to be recorded on CRFs. Documentation of viral loads other than the screening value shall be defined using the assay in use at the time ( $<50$  copies/mL or  $<400$  copies/mL).

### Medical History

The medical history must include all AIDS-related diagnoses and any history of coronary artery disease, congestive heart failure, renal disease, hypertension, diabetes, or stroke. ACTG diagnostic criteria will be provided in the Manual of Operations to aid in documentation. Any allergies to any medications and their formulations must be documented. Surgeries that are planned prior to the time of the subject's informed consent will also be documented. Current and previous smoking history will also be collected.

### Medication History

A medication history must be recorded in the source documents and the CRF. The medication history will include the following:

- Complete HIV treatment history, including start and stop dates of any current or past antiretroviral medication (estimated if the exact dates cannot be obtained), immune-based therapy, or HIV-related vaccines, including blinded study medications.
- Complete treatment history of any prescription medications taken for the treatment or prophylaxis of opportunistic infections, including actual or estimated start and stop dates.
- All prescription medications (in addition to those noted above) taken in the 30 days prior to study entry, including actual or estimated start and stop dates. Only dosages for ART will be required.
- Nonprescription medications taken in the 30 days prior to study entry. Include actual or estimated start and stop dates.
- Alternative therapies and dietary supplements taken in the 30 days prior to study entry. Include actual or estimated start and stop dates.

### Complete Physical Exam

A complete physical examination is required at screening and includes: examination of the skin, head, mouth, and neck; auscultation of the chest; cardiac exam; abdominal exam; examination of the lower extremities for edema. The exam also includes measurement of mid-waist and hip circumferences, a waist/hip ratio calculation, and documentation of signs and symptoms, diagnoses, vital signs (temperature, pulse, respiration rate, and blood pressure), height, and weight. In addition, the exam includes an assessment (and subject reported changes) of neck fat, breast enlargement, lipomas, and peripheral lipoatrophy.

### Targeted Physical Exam

A targeted physical examination at visits for Weeks 0-24 is to be driven by any previously-identified or new signs or symptoms that the subject has experienced since the last visit. Weight, vital signs (temperature, pulse, respiration rate, and blood pressure), and diagnoses will also be collected at all visits.

### Height

Height in stocking feet will be recorded on the CRF at the screening visit only.

### Signs and Symptoms

At entry, record all signs and symptoms occurring in the 30 days prior to entry. After entry, record all signs and symptoms  $\geq$  Grade 2. This study will use the DAIDS toxicity grading system (see Manual of Operations). Any signs or symptoms that led to a change in the study drug (telmisartan), regardless of grade, must be recorded.

### Diagnoses

Record all diagnoses identified by the ACTG Criteria for Clinical Events and Other Diseases (see Manual of Operations). All confirmed and probable diagnoses made since the last visit will be recorded.

### Concomitant Medications

All concomitant medications taken since the last visit will be recorded as a running list in the source documents. Only prescription medications and method of birth control (where applicable) will be recorded on the CRFs.

### Antiretroviral Medications

All modifications to antiretroviral medications including doses and subject- or physician-initiated interruptions, modifications, or permanent discontinuation will be recorded on the CRFs.

### Study Treatment Modifications

Modifications to telmisartan dosing, schedule, interruptions, or permanent discontinuation will be recorded on the CRFs. If a subject misses more than 4 consecutive doses, the study treatment is considered modified and this must be reported appropriately on the CRF.

### CT Scan

Single-slice CT abdomen at the level of L4/L5, with measurement of visceral and subcutaneous fat, will be read centrally by Tufts University. Please see Manual of Operations for instructions.

## **6.6. Laboratory Evaluations**

Fasting will be required for study entry, Week 12, and Week 24. Fasting will be defined as nothing by mouth except water and medications for at least 8 hours prior to the lab draw. At screening and entry, all laboratory values must be recorded on the CRFs regardless of grade. For post-entry assessments, record all laboratory values  $\geq$  Grade 2. Any laboratory value that led to a change in study treatment (telmisartan), regardless of grade, must be recorded. Fasting lab studies include: total cholesterol, LDL cholesterol, triglycerides, HDL cholesterol, glucose, and insulin.

**Sites must refer to the Division of AIDS Table for Grading the Severity of Adult and Pediatric Adverse Events** (see Manual of Operations), **Version 1.0, December 2004, to establish grading.**

The table is available on the telmisartan study website at  
<http://www.uclacarecenter.org/MATHtrial.org>.

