#### Fasting lipids, Glucose, Insulin, hsCRP

Total cholesterol, HDL cholesterol, LDL cholesterol (direct), triglycerides, hsCRP, and glucose will be performed at entry and weeks 12 and 24 in real time at the local laboratory. Insulin will be batched and analyzed at the end of the study.

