### **9.4 Secondary Endpoint Assessments (Change in below calculated between Weeks 0 and 24)**

- Abdominal SAT and VAT:SAT ratio, as calculated from single slice CT scan (as above)
- Total cholesterol, HDL cholesterol, triglycerides, LDL cholesterol (direct)
- Markers of inflammation

- Insulin, glucose, HOMA-IR
- Framingham Risk Score calculation
- Prevalence of metabolic syndrome
- Systolic and diastolic blood pressure measurements
- Urinary protein excretion and serum creatinine measurement

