## 10.0 DATA COLLECTION, MONITORING, AND ADVERSE EVENT REPORTING

### 10.1 Records to Be Kept

Data will be collected onto Case Report Forms (CRFs) provided by the Data Management Center at UCLA, and will be labeled only with a subject's study ID number. CRFs will be stored in a locked cabinet available only to study personnel for a period of time determined by pertinent policies and regulations, and for at least two years after study discontinuation.

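### After entry, Section 6.6 requires CRF recording only of laboratory values of Grade 2 or worse (or that changed telmisartan), yet Section 9.4 needs every subject's Week 24 lipids, glucose and creatinine

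*Protocol*

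**What the plan says.** Protocol Section 6.6 (Laboratory Evaluations) sets different recording rules before and after treatment starts.

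- Before: "At screening and entry, all laboratory values must be recorded on the CRFs regardless of grade".
- After: "For post-entry assessments, record all laboratory values", with the sentence ending in a threshold of Grade 2 or above.
- One addition after entry: "Any laboratory value that led to a change in study treatment (telmisartan), regardless of grade, must be recorded".

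The same paragraph continues: "Fasting lab studies include: total cholesterol, LDL cholesterol, triglycerides, HDL cholesterol, glucose, and insulin". The rule and the endpoint analytes therefore stand together.

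The 6.6 subsection on fasting lipids, glucose, insulin and hsCRP says that the lipids, hsCRP and glucose "will be performed at entry and weeks 12 and 24 in real time at the local laboratory". Insulin is held back and batched at the end of the study. Serum creatinine belongs to the safety laboratory panel, which is also run locally.

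Section 9.4 defines the secondary endpoints as change between Weeks 0 and 24. They include the four lipid measures, inflammation markers, insulin with glucose and HOMA-IR, Framingham score, metabolic syndrome prevalence, and "Urinary protein excretion and serum creatinine measurement". Section 10.1 names the CRF as the form on which study data are collected.

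**The concern.** A paired change needs both values from each subject. The protocol guarantees the Week 0 value and makes the Week 24 value compulsory only if it is bad enough, or if it altered study treatment. Both conditions depend on the outcome, so what is missing is not missing at random.

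The secondary objectives at stake are 1.3.3 (lipids), 1.3.4 (insulin sensitivity, through glucose), 1.3.6 (Framingham score), 1.3.7 (metabolic syndrome) and the creatinine part of 1.3.9. The hsCRP part of 1.3.5 is exposed to a lesser degree. Section 9.1 raises enrolment from 27 to 35 partly to give more power for secondary endpoints, and that gain is lost for any analyte whose Week 24 values are not captured. The trial has a single arm, so there is no control group subject to the same filter against which a distortion might cancel.

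**Working it through.** **Step 1. Which endpoint analytes fall under the rule.** Section 9.4 set against Section 6.6:

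| Endpoint in 9.4 | How obtained (6.6, 6.1) | Governed by the post-entry grade rule? |
|---|---|---|
| Total, LDL and HDL cholesterol, triglycerides | Local laboratory, real time, entry and Weeks 12 and 24 | Yes |
| Glucose | Local laboratory, real time, same visits | Yes |
| HOMA-IR | Needs glucose and insulin | Yes, through glucose |
| Serum creatinine | Local safety laboratory | Yes |
| Framingham score, metabolic syndrome | Derived; the protocol gives no formula, but both are customarily built partly from lipids, and metabolic syndrome also from glucose | Yes, through their laboratory components |
| Inflammation markers | hsCRP locally; CRP and others also from stored samples | Partly |
| Insulin | Batched at study end | No |
| Urinary protein | Urine collected at baseline and Weeks 12 and 24; not stated to be a graded local result | Not shown |
| Blood pressure | Vital signs, all visits | No |
| Abdominal SAT and VAT:SAT ratio (and primary VAT) | Central CT reading | No |

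**Step 2. Is there an exemption?** The subsections on lipids and on safety laboratories say where and when the tests are run. They do not say that all results are recorded. The one exception in 6.6, for values that changed telmisartan, is itself selective and does not restore the missing normal results.

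**Step 3. What exact compliance yields.** At Week 0 all 35 values are required. At Week 24 the required values are those of Grade 2 or above plus those that changed treatment. If the grading table, which is not reproduced in the protocol, has no Grade 2 level for an analyte, the threshold would require no Week 24 value for it at all.

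**Step 4. Size, as illustration only.** The protocol gives no laboratory means, standard deviations, Grade 2 frequencies or within-subject correlations, so every input here except N = 35 is an assumption. Take an analyte with no true change, standardised Week 0 and Week 24 values that are bivariate normal with correlation r, and only the top fraction p of Week 24 values recorded.

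- Expected number recorded = 35 × p.
- Mean recorded Week 24 value = m(p), the mean of the top fraction p of a standard normal.
- Expected Week 0 value in the same subjects = r × m(p).
- Apparent change = (1 − r) × m(p).

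With p = 10%: 35 × 0.10 = 3.5 recorded, m = 1.755. With p = 20%: 35 × 0.20 = 7 recorded, m = 1.400. For r from 0.6 to 0.8, the apparent worsening runs from (1 − 0.8) × 1.400 = 0.28 SD to (1 − 0.6) × 1.755 = 0.70 SD.

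Fixing the cutoff instead at +1, +1.5 or +2 SD gives 5.6, 2.3 or 0.8 expected records out of 35. With r from 0.5 to 0.9, the apparent change runs from 0.15 SD (cutoff +1, r = 0.9) to 1.19 SD (cutoff +2, r = 0.5).

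The direction is the same throughout, but the size moves about eightfold (1.19 / 0.15) with inputs the protocol does not supply. No single figure should be attached to this point.

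**The case against.** The strongest reply is that the Grade 2 threshold is a minimum and does not bar a site from recording more. It parallels the rule for signs and symptoms in Section 6.5 and refers to a severity table, so it can be read as adverse-event capture that was never meant to govern endpoint data. Section 10.2 leaves CRF instructions to the data management center, and neither the CRF nor the Manual of Operations is at hand; the Week 24 form may already have a field for every analyte. The trial has one site and 35 subjects, the tests are scheduled for everyone, and Section 10.3 gives the monitor access to supporting data and medical records. The affected endpoints are secondary, in a pilot whose analyses Section 9.6 calls exploratory.

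Most of this stands, and it limits the claim. A reader might infer that the Week 24 endpoints will be lost, or that the trial will make telmisartan look harmful. The documents support neither. Loss is what exact compliance permits, not what must happen. A biased result would further require someone to analyse the few recorded pairs while the other results sat uncollected in laboratory reports. Nor can the filter be extended to all laboratory endpoints: insulin is batched, CRP can be measured from banked samples, and urinary protein is not shown to be a graded local result. HOMA-IR is also listed among the stored-sample measurements, but glucose itself is not named there and is said to be run in real time.

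The reply does not remove the defect. The contrast with the entry rule, where grade is expressly irrelevant, shows that the distinction is deliberate. A CRF instruction asking for every value would go beyond the protocol's stated requirement, so the protocol text is still the place to correct it. No analysis plan can use values that were never captured.

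**Conclusion.** The point holds as a conflict between a stated recording rule and stated endpoints. For lipids, glucose and serum creatinine, and for HOMA-IR, Framingham score and metabolic syndrome through them, Section 6.6 does not secure the Week 24 values that Section 9.4 needs, and what it does require is selected on the outcome. hsCRP is partly exposed. Primary VAT, the other CT measures, blood pressure and batched insulin are outside the problem.

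The bias cannot be quantified from the document; the ranges in the working show its direction and mechanism only. The conclusion rests on two readings: that the rule covers all laboratory values in 6.6, since no exemption is given, and that the CRF is the route into the database, as Section 10.1 indicates. This should be fixed, but because the values are probably recoverable and the endpoints are secondary and exploratory, it does not threaten the trial's main result.

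**What to change.** Add to Section 6.6 that all Week 24 results for total, LDL and HDL cholesterol, triglycerides, glucose, hsCRP and serum creatinine are recorded on the CRF regardless of grade. Extend this to Week 12 only where those results will be analysed, since Section 9.4 defines change between Weeks 0 and 24. Confine the Grade 2 threshold to the other post-entry safety laboratory values, and keep the provision for values that changed telmisartan. Check that the CRF and the Manual of Operations agree with the amended text. For subjects already past these visits, enter the missing results from the local laboratory reports.

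The cost is one amended paragraph and a little extra data entry for 35 subjects. The tests are already scheduled for everyone, so no extra sampling or assay is needed and the sample size does not change.
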